#### 3.2.1. Participants and Recruitment

The study population is a sub-cohort of the participants in a cohort from the Mexico City metropolitan area (35). It is a prospective longitudinal study in which clinically healthy residents of Mexico City, between 20 and 50 years old are recruited to be evaluated every 2 years for a period of 10 years or until they develop hypertension. Anthropometric (weight, height and waist circumference), clinical and biochemical parameters (blood and urine laboratory tests with markers such as glucose, cholesterol, triglycerides, sodium and potassium, etc.), nutritional and lifestyle habits (physical activity, sleep quality, alcohol and tobacco consumption) and social determinants of health are assessed (Supplementary Material). All participants are measured periodically (every 2 years) by a battery of specific serum biomarkers of systemic inflammation. Participants will be contacted every 6 months via email or by telephone to assess their medical and dental history including treatment for hypertension and/or periodontitis, as well as any medication (including antibiotic treatment) used over the previous months (see Figure 1).

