### 3.3. Sample Size

#### 3.3.1. Sample Size for Periodontitis and Incidence of Hypertension

The projected sample size for periodontitis and incidence of hypertension will be 1212 individuals from those participating in the umbrella cohort. A logistic regression (LR) for a binary response (hypertension) on an independent variable (periodontitis) with a sample size of 866 participants (90% of whom are in group X = 0 and 10% are in group X = 1) achieves 90% power with 0.05 significance to detect a change in the Probability (Y = 1) of an estimated value of incidence of hypertension of 21.5%. This change corresponds to a Relative Risk (RR) of 2.4 (a RR between 1 and 2.74 has been reported) (6, 30, 36). An adjustment was made since the multiple regression of the variable of interest in the other independent variables in the LR obtained a *R*^2^ of 0.3. A 40% dropout rate is expected (*n* = 346), so the projected sample size will be 1,212 people.

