#### 3.4.3. Elimination Criteria

People who develop hypertension and initiate and/or maintain regular and active antihypertensive therapy.People who develop systemic and uncontrolled diseases that may interfere with the severity of periodontitis.People who initiate and maintain regular and active periodontal treatment during the study follow-up.People who develop some forms of periodontitis that require regular antibiotics.People who undergo dental procedures that involve implant placement.

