## 5. Oral Health Diagnosis

Participants will be evaluated every year using standardized and valid clinical measurements to identify the presence of periodontitis (see Figure 1). All participants will receive detailed information about their oral health following each evaluation and will be referred to specialized periodontal treatment whenever needed, particularly if they have severe disease. Receiving periodontal treatment, however, will depend only on each participants' decision. It should be noted that our research group will not carry out any clinical intervention or pharmacological prescription. This statement is mentioned in the informed consent for the present study.

Those participants who have started phase I periodontal therapy (scaling and root planing) and have not given it continuity (at least a couple of maintenance visits every 3 months) during the follow-up (between one evaluation and another carried out by our group) *will continue to be included in the study*. End of follow-up will be given to those participants who undergo systematic and regular periodontal treatment (at intervals of 2, 3, or 4 weeks for more than 3 months) or with forms of refractory or progressive periodontal rupture, periodontitis in a rapid rate of progression, necrotizing periodontal diseases or periodontal abscess that require regular taking of antibiotics (73–75) (see Figure 1).

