#### 9.1.2. Longitudinal Analysis

As part of the longitudinal analysis the incidence of each oral variable included in the study in 30-month periods will be evaluated. Similarly the relative risk for each oral variable included will be evaluated according to different variables considered as risk factors (alcoholism, smoking, among others) through bivariate and multivariable analyses, using generalized linear models, logistic regression models, and multinomial regression models.

Starting with the third evaluation (baseline evaluation + first follow-up + second follow-up), trajectories of oral health conditions will be identified. From these variables associated with each one will be identified (gender, marital status, occupational class, age, education, among others). In the same way trajectories will be considered as risk factors for the development of hypertension in the study participants and will be included in neural network models.

For the statistical association analysis, participants will be classified in two groups: Group 1: without periodontitis and Group 2: with periodontitis (including all those participants that according to the CDC/AAP have mild, moderate, or severe periodontitis). For the sake of this association analysis and by following the consensus of the literature (73–75), participants in Group 2 who start periodontal treatment but do not continue with it until remission will be kept in this group and considered with periodontitis. However, a note will be made with details on the type, the extent of their treatment and the effects on their periodontal health, derived from their periodical periodontal evaluation.

This information will be used for a further *a posteriori* analysis. The information about the extent of their periodontal disease (mild, moderate and severe) will be also considered a posteriori. It is worth noticing that *a posteriori cluster analysis*, for instance, Propensity Score evaluation (93, 94) is not unusual in prospective observational studies subject to constraints, as is this case (95–99).

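### Ending follow-up when regular periodontal treatment starts removes mainly exposed participants after baseline and can bias the periodontitis–hypertension association in a direction the plan does not fix

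*Protocol article*

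**What the plan says.** Periodontitis is the exposure and incident hypertension the outcome (Protocol article, section 3.2). One specific goal in section 2.2 relates 60-month hypertension incidence to periodontitis present at baseline. The first hypothesis in section 2.3 concerns people with periodontitis and does not restrict it to untreated disease.

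Under section 5, participants are examined yearly, told their results, and "will be referred to specialized periodontal treatment whenever needed, particularly if they have severe disease". Uptake is left to the participant. Section 5 then states: "End of follow-up will be given to those participants who undergo systematic and regular periodontal treatment". The same sentence ends follow-up for refractory, rapidly progressing and antibiotic-requiring forms. Section 3.4.3 lists as grounds for elimination: "People who initiate and maintain regular and active periodontal treatment during the study follow-up".

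In section 9.1.2, mild, moderate and severe disease form one exposed group, and "participants in Group 2 who start periodontal treatment but do not continue with it until remission will be kept in this group". Severity and treatment details are left to a posteriori work, where propensity scores are named as an example. The limitations in section 12.1 do not mention this removal.

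On available data, umbrella-cohort members are "evaluated every 2 years for a period of 10 years or until they develop hypertension" (section 3.2.1). They are contacted every six months about treatment, and section 8 takes the hypertension registry from the umbrella cohort.

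**The concern.** Whether someone stays in follow-up depends on something that happens after baseline, is a consequence of the exposure, and is prompted by the study's own referral. Participants without periodontitis have little reason to meet the rule. Among those with periodontitis, the referral wording points to the more severe cases, and uptake selects those who seek care. Both traits may predict hypertension. The protocol's introduction itself links treatment of severe periodontitis to better endothelial function.

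At stake is the main epidemiological contrast. The exposed group still followed at 60 months may differ from the one enrolled, and the estimate then depends on how removed participants are handled. The planning split makes exposed participants scarce: "90% of whom are in group X = 0 and 10% are in group X = 1". The 40% dropout allowance in section 3.3.1 is not divided by exposure or reason, so it does not show that differential loss was considered.

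**Working it through.** **1. Reproducing the plan's figure.** Inputs from section 3.3.1: "with a sample size of 866 participants", "achieves 90% power with 0.05 significance", 10% exposed, RR 2.4, incidence 21.5%. Reading 21.5% as the exposed risk, p1 = 0.215 and p0 = 0.215/2.4 = 0.0896. With B = 0.10, P = 0.9 × 0.0896 + 0.1 × 0.215 = 0.1021. For a logistic model with one binary covariate, two-sided 0.05:

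N = [1.96 √(P(1−P)/B) + 1.2816 √(p0(1−p0) + p1(1−p1)(1−B)/B)]² / [(p1−p0)²(1−B)]
= [1.96 × 0.9576 + 1.2816 × 1.2651]² / [0.1254² × 0.9] = 864.4, against 866 stated.

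This match does not apply the R² of 0.3. The figures below are on the same basis.

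**2. One worked scenario.** The documents give no severity mix, uptake or risk by severity, so all of these are assumed: 30% of the exposed severe with 35% risk, the others 15.7% (average 0.3 × 0.35 + 0.7 × 0.157 = 0.215); 60% of severe and 10% of others removed; none of the unexposed.

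- *Removed before any event.* Kept = 0.3 × 0.4 + 0.7 × 0.9 = 0.75. Events = 0.12 × 0.35 + 0.63 × 0.157 = 0.1409. Risk = 0.1409/0.75 = 0.188. RR = 0.188/0.0896 = 2.10.
- *Removal spread evenly over 60 months, earlier events kept, the rest dropped.* About half the events among those removed come first: 0.5 × (0.18 × 0.35 + 0.07 × 0.157) = 0.0370. Risk = (0.1409 + 0.0370)/(0.75 + 0.0370) = 0.226. RR = 2.52 (2.55 with constant hazards).
- *Same timing, removed participants counted as non-events.* Risk = 0.1409 + 0.0370 = 0.178. RR = 1.99.
- *Earlier events kept, but all removal within two years, or within one.* RR = 2.30 or 2.20 (constant hazards).
- *Person-time analysis, even removal, censored.* Rate ratio 2.44 against 2.58 without removal.

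**3. Range over assumptions.** Closed form: severe share 10–50%, severe-to-other risk ratio 1–2, uptake 30–70% in severe and 5–10% in others, so 7.5–40% of the exposed are removed.

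| Handling of removed participants | RR (design 2.40) |
|---|---|
| Leave before any event | 2.00–2.40 (2.40 if severity is not prognostic) |
| Removed at mid-follow-up, counted as non-events | 1.80–2.31 |

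Simulation with removal over time, severe share 30%, 11–33% of the exposed removed:

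| Analysis | Without removal | With removal |
|---|---|---|
| Binary, earlier events kept, rest dropped | about 2.40 | 2.50–3.01 |
| Binary, counted as non-events | about 2.40 | 2.02–2.25 |
| Rate ratio, censored | about 2.58 | 2.45–2.72 |

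When neither severity nor the uptake-related trait is prognostic, the rate ratio stays at 2.58–2.59, but the binary analysis keeping earlier events still gives 2.63–2.78.

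**4. Power.** With n0 = 779.4 unexposed, n1 = 86.6 × (1 − loss) exposed and P̄ the pooled risk:

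power = Φ{[(p1−p0) − 1.96 √(P̄(1−P̄)(1/n1+1/n0))] / √(p1(1−p1)/n1 + p0(1−p0)/n0)}

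| Exposed lost | n1 | Power |
|---|---|---|
| 0% | 86.6 | 90.0% |
| 20% | 69.3 | 84.8% |
| 30% | 60.6 | 81.2% |

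**5. The treatment rules side by side.** Section 5 keeps those who began phase I therapy without continuity, with continuity described through three-monthly maintenance visits. It ends follow-up for treatment at intervals of two to four weeks lasting more than three months. Someone who does continue three-monthly maintenance meets neither rule. Section 9.1.2 turns on remission instead, and assigns an analysis group rather than deciding retention. Section 3.4.3 speaks of elimination and section 5 of end of follow-up, which could mean exclusion or censoring.

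**The case against.** The strongest defence is that the restriction is coherent. Section 3.4.2 excludes people under regular periodontal treatment at entry, and section 3.4.3 carries that through follow-up, so the intended exposure may be periodontitis without regular treatment. Keeping treated participants as exposed could dilute the contrast. This is a legitimate secondary question. However, sections 2.2 and 2.3 do not state it as the target, and it would need removal to be independent of risk given modelled covariates. The article describes no such method for the association analysis.

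Four stronger readings are tempting, and the objection to each stands.

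- A reader might infer a known attenuation. That requires removal before any event or counting as non-events. Removal follows yearly referral and more than three months of treatment, so it is spread over time, and with earlier events kept the same inputs can give an inflated RR.
- A reader might infer that outcomes of removed participants are lost. The documents do not say whether these people are censored, dropped or still covered by the umbrella registry.
- A reader might take removal of severe cases as established. It is inferred from the referral wording. The end rule is narrow, uptake is voluntary, and participants without baseline periodontitis are also re-examined and can be referred.
- A reader might conclude that three rules each classify a participant on three-monthly maintenance differently. The text shows a gap between the two section 5 rules. Figure 1, which section 5 cites and which is not shown, may fill it.

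The 10% exposed share is also only a planning input. A higher prevalence would make each loss less costly.

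**Conclusion.** The point holds as a risk of bias of undetermined direction. Follow-up ends after baseline for a reason tied to the exposure, and the article neither corrects for this nor lists it as a limitation. Under the assumptions shown, the design RR of 2.4 becomes about 2.0–2.3 (1.8 at the extreme) or about 2.5 and above, according to the timing and handling of removals. A person-time analysis is generally less affected and is biased only if severity or health-seeking predicts hypertension and is not modelled. Power falls to about 85–81% if 20–30% of some 87 exposed are lost beyond what the 866 already allows. The mechanism rests on the text; every magnitude rests on assumed severity mix, uptake and risks. The change should be made, because it is cheap and the outcome data appear to be within reach.

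**What to change.** - Do not end hypertension ascertainment when periodontal treatment starts. Keep using the umbrella cohort's two-yearly blood pressure data and registry, and the six-monthly contacts.
- Make the main analysis by baseline periodontitis status regardless of later treatment.
- Give the untreated-periodontitis contrast as a sensitivity analysis: censor at treatment start, with inverse-probability-of-censoring weights built from yearly severity and other collected predictors of uptake. Do not adjust for treatment as an ordinary time-varying covariate, because that conditions on a consequence of the exposure.
- Report removals and treatment uptake by baseline severity.
- Reconcile elimination in section 3.4.3 with end of follow-up in section 5, and the section 5 and 9.1.2 wording, so that continued three-monthly maintenance is covered by one stated rule.

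This alters follow-up and analysis, not anyone's care. The cost is protocol wording and one sensitivity analysis, with no new visits if the umbrella data are used. The downside is that the main contrast will include some treated periodontitis, which may dilute it; the sensitivity analysis addresses that.

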### 5.1. Methods Collection

Sampling of saliva and subgingival plaque will be performed at baseline and at the end of follow-up in the participants selected for the oral microbiome analysis. All participants will be asked to stop taking antibiotics 3 months before and to stop mouthwashes—1 week before the clinical examination. History of occasional antibiotic consumption (outside sampling dates) will be recorded and analyzed. They will also be asked to stop tooth brushing 24 h before the clinical exam. They will be asked to refrain from eating, drinking anything other than water and chewing gum for 12 h prior to taking samples (76).

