#### 3.3.2. Sample Size for the Microbiological Studies

The sample size of the oral and subgingival microbiome study is projected to be 200 people sub-sampled in a randomized adjusted cohort design (100 subjects with periodontitis and 100 without periodontitis). This is so since the lower bound for the number of samples to probabilistically infer co-existence networks (in this case of microbial species) by the method we use (based on the calculation of the mutual information function) is ~100 per evaluated group (37). A total of 400 microbial samples per evaluation time (baseline and 60 follow-up months) will be placed 200 for periodontal health subjects and 200 for periodontitis subjects, with a subdivision of 100 for saliva and 100 subgingival samples each. Since the sequencing analysis for microbiota is relatively expensive it was decided to use just this number for experimental design. Sampling for microbiome analysis will be done in participants who have developed hypertension (with periodontitis and without periodontitis) and in those who have remained at normal blood pressure levels (with periodontitis and without periodontitis).

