##### 3.6.1.2. Blood Pressure Measurement Plan According to Office Blood Pressure Levels

Repeated examination and/or measuring BP levels at home will be performed as follows:

Participants with normal BP (<130/ <85), will be re-examined on at least one further office visit (1–2 week intervals).Participants with suspected high-normal BP (130–139 and 85–89), will have repeated office visits (2 at 1–4 week intervals) required and will be asked to monitor blood pressure for at least 5 (preferably 8) consecutive days at home (HBPM).Participants with suspected hypertension (≥140 and ≥90), repeated office visits (3 or 4 visits at 1–4 week intervals) for re-examination will be required. Also, they will be asked to monitor blood pressure for 8 consecutive days at home (HBPM). Those diagnosed with HBP during this period (see HBPM below) will be referred to the ambulatory blood pressure monitoring (ABPM) service at the INC-ICh.The diagnosis will be made on a single visit, if BP is ≥180/≥110 mm Hg on the first set of three measurements. Then the participant will be immediately scheduled for a clinic visit at the INC-ICh to receive appropriate treatment. The day of the diagnosis of hypertension will be considered the date of disease onset.

Participants who are diagnosed with HBP at another facility at any time during the study will be requested to immediately notify principal investigators. These participants will be asked to schedule a visit at the INC-ICh prior to starting any medical treatment, to confirm the diagnosis and to complete the “end of the study” visit. Also, participants who are diagnosed with HBP and initiate and maintain regular antihypertensive therapy (more than 2 weeks) will be eliminated, according to the criteria of the umbrella cohort (35). The date of disease onset will be considered as the date of confirmation of the diagnosis and/or the date of initiating antihypertensive therapy.

For those diagnosed with HBP during one of the follow-up visits at INC-ICh, the date of disease onset will be recorded as the date of the visit. Additionally, all participants will be contacted by telephone or by email every 6 months to verify whether they have been diagnosed with HBP and/or if they are taking antihypertensive therapy (see Figure 1).

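### The second microbiome sample has two conflicting times for people who develop hypertension, so the follow-up comparison either mixes hypertension with elapsed time or loses treated cases

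*Protocol article*

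**What the plan says.** Two sections give the time of the second microbiome sample.

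- Section 5.1 says sampling takes place "at baseline and at the end of follow-up in the participants selected for the oral microbiome analysis". It names no month and does not separate cases from non-cases.
- Section 3.3.2 says "A total of 400 microbial samples per evaluation time (baseline and 60 follow-up months"), so it fixes month 60 for all. The subset is "100 subjects with periodontitis and 100 without periodontitis".

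Section 3.3.2 also names the groups: "Sampling for microbiome analysis will be done in participants who have developed hypertension (with periodontitis and without periodontitis"), and likewise those whose blood pressure stayed normal.

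Other sections determine when a case's follow-up ends.

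- Section 3.2.1: umbrella-cohort participants are "evaluated every 2 years for a period of 10 years or until they develop hypertension".
- Section 3.6.1.2, on people diagnosed at another facility: "These participants will be asked to schedule a visit at the INC-ICh prior to starting any medical treatment". The purpose is to confirm the diagnosis and complete the end-of-study visit.
- Sections 3.4.3 and 3.6.1.2: cases who start and maintain regular antihypertensive therapy are eliminated.
- Section 5: follow-up also ends for people who take up regular periodontal treatment, so some non-cases stop before month 60 as well.

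**The concern.** End of follow-up is a personal date in this protocol, and for a case it falls at or near diagnosis. Month 60 is a calendar date common to all. The two coincide for completing non-cases and differ for most cases.

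If cases are sampled near diagnosis and completing non-cases at month 60, the groups differ at the second sample in time since baseline, and with it in ageing and periodontal progression. Drift in the oral community over time could then look like a hypertension signature, or hide one. If month 60 governs instead, the hypertension groups lose the treated cases.

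The contrast matters because section 2.1 makes the primary endpoint the association of subgingival microbiome profiles with the presence of hypertension and periodontitis, and section 3.4.1 admits only people without hypertension. No baseline sample can therefore come from a hypertensive person. Only the second sample shows the microbiome while hypertension is present.

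**Working it through.** **The plan's own count.** 2 periodontal groups × 100 people × 2 sample types = 400 samples per evaluation time. This reproduces the stated 400, so the question is timing, not number.

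**What each rule gives**

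- Completing non-case: month 60 under both sections.
- Case, section 5.1 read with 3.2.1 and 3.6.1.2: at or near diagnosis.
- Case on regular therapy, section 3.3.2 read with 3.4.3: eliminated before month 60, so no second sample.
- Non-case who takes up regular periodontal treatment: before month 60 under 5.1; no month-60 sample under 3.3.2.

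**Size of the time gap under the section 5.1 reading.** Diagnosis times are assumed. Trying 18 to 100 cases among 200, with diagnoses at months 24/48, at months 24/48/60, or spread over follow-up, and all non-cases at month 60:

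- Cases are sampled on average about 16 to 30 months earlier.
- R² between hypertension and sampling time is about 0.37 to 0.79, so VIF = 1/(1 − R²) is about 1.6 to 4.7.
- If 20% of non-cases end early (assumed), VIF is about 1.05 to 1.6.

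One case by hand, with 43 cases (half at month 24, half at month 48) and 157 non-cases at month 60:

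- Between-group variance of time = (43 × 157/200²) × 24² = 97.2.
- Within-group variance = (43/200) × 12² = 31.0.
- R² = 97.2/128.2 = 0.76 and VIF ≈ 4.1, so the standard error roughly doubles (√4.1 ≈ 2.0).

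**Unadjusted follow-up test, for illustration.** There are two case counts.

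- 43 cases: 200 × 0.215, applying the planned 21.5% to everyone.
- 30 cases: 100 × 0.215 + 100 × (0.215/2.4) = 21.5 + 9.0. This treats 21.5% as the risk with periodontitis. On that reading the two-sided two-group formula, before any R² adjustment, gives 865 against the plan's 866.

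Assume a mean gap of 24 months, no hypertension effect, and linear drift of D SD over 60 months. Spurious difference = D × 24/60. Non-centrality = difference × √(n₁n₀/(n₁+n₀)). The test is two-sided at 5%.

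- D = 0.25 (difference 0.10 SD): 8.9% with 43 v 157; 8.0% with 30 v 170.
- D = 0.5 (0.20 SD): 21.3%; 17.3%.
- D = 1 (0.40 SD): 64.2%; 52.4%.

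**Does adjustment recover the level?** Simulation with 43 v 157, change from baseline as outcome, within-person correlation 0.5 (assumed) and no hypertension effect. The unadjusted standard error is about 0.17.

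- Elapsed time plus hypertension, line through the origin, linear drift: rejects about 5% at all three drifts, standard error 0.16.
- Same model, curved drift reaching 1 SD at month 60: about 17–18% if drift follows the square root of time, 24% if it follows the square.
- Free intercept added: about 5–7% across these shapes, but standard error about 0.35, roughly double the unadjusted value.

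**The case against.** The strongest reply is that no section states that cases are sampled at diagnosis. Section 3.3.2 fixes month 60 without exception. The rule on following people until hypertension describes the umbrella cohort. The end-of-study visit is described for people diagnosed elsewhere and takes place at the cardiology institute, whereas oral samples are taken at the dental school (section 4). Figure 1 outlines follow-up scenarios by participant role and is not shown here. This stands: the schedule is an inference from several sections. What the text itself establishes is the conflict between 3.3.2 and 5.1.

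A reader might go further and infer that time and hypertension are inseparable, so that no model term can help. The documents do not support that. Everyone in the subset has a baseline sample, diagnosis times vary among cases, and some non-cases end early. Under linear drift a change-from-baseline model holds the 5% level without loss of precision. What remains is dependence on the shape of drift, or a doubled standard error if that assumption is relaxed. Non-cases who end early because of periodontal treatment or aggressive disease are also doubtful controls for time, since those reasons relate to the microbiome.

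A reader might also infer that the whole microbiome programme is compromised. It is not. Section 2.2 relates 60-month incidence to the baseline microbiome, which second-sample timing cannot touch, and neither hypothesis 3 nor the primary endpoint names the follow-up sample as its basis.

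Finally, the false-positive figures assume a drift the documents do not give and an unadjusted test they do not specify; section 9.2.4 lists Cox and multivariable models. That is right, and the figures are illustrations only.

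**Conclusion.** The concern holds in limited form. Sections 3.3.2 and 5.1 conflict for people who develop hypertension and must be reconciled, together with 3.2.1, 3.4.3 and 3.6.1.2. As written, cases are either sampled earlier than completing non-cases or, if treated, are gone by month 60, and nothing aligns the times for a contrast the protocol plans.

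Under the section 5.1 reading and the assumed diagnosis times, the gap averages about 16 to 30 months when all non-cases complete. If it is ignored, the false-positive rate depends on drift: modest at 0.25 SD over 60 months (8–9%) and large at 1 SD (52–64%). Adjustment is feasible but either imprecise or reliant on the assumed shape of drift, because sampling times overlap poorly. If diagnoses fall only at months 24 and 48 and all non-cases complete, the second-sample times do not overlap at all. The problem is confined to the follow-up comparison.

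**What to change.** - Rewrite sections 3.3.2 and 5.1 to give one second-sample time for cases and one for non-cases, consistent with the rules on end of follow-up and elimination.
- Name the baseline samples as the basis for testing hypothesis 3.
- For the follow-up contrast, choose one of two routes. (a) Take each non-case's second sample at the existing yearly oral visit that matches a case's elapsed time, within the same periodontitis group; this removes the time gap. (b) Keep month 60 for non-cases, analyse change from baseline with elapsed time in the model, and label the contrast descriptive.
- Under either route, report sampling time by group.

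The cost is mainly wording and a sampling calendar; non-cases already attend yearly and the number sequenced need not rise. Route (a) yields fewer month-60 samples for describing 60-month change and needs a rule for matched non-cases who later become cases. Any plan to sample at diagnosis needs an oral sampling appointment linked to the diagnosis visit, since the two happen at different institutions. Settle this before follow-up sampling begins: a sample missed at diagnosis cannot be recovered.
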